#### Blood fatty acid composition.

At baseline and after 8 weeks of supplementation, a fasting capillary blood sample from a fingertip will be collected and sent to OmegaQuant Analytics for blood FA composition analysis [32].

### Subconcussion intervention

A standardized and reliable soccer heading protocol will be used for the experiment. The ACT Head Impact Tracker head sensor Pro, embedded in a head-band pocket and positioned directly below the external occipital protuberance (inion) will be used to monitor linear and angular head accelerations. A JUGS soccer machine will be used to simulate a soccer throw-in with a standardized ball speed of 30 mph. Subjects will stand approximately 40 ft away from the machine to perform the heading [33]. Participants perform 20 headers with 1 header per 30 seconds. Both groups will undergo additional heading sessions 24 hours after the first session. The participants will be instructed to direct the ball in the air back toward the research staff standing 20ft in front of the participant. If the participant fails to return the ball in the air and/or within 60° in front, which will result in a low head acceleration, they will re-do the header.

### Measurements

#### Baseline measures.

The following information will be assessed at baseline: SCID-5-RV [34] for psychiatric diagnosis, blood spot for assessment of omega-3 FA compositions [32], dietary recall for estimation of antioxidant levels [35], clinical measures, demographic questionnaire, and medical and concussion history questionnaires. Participants will also complete the alcohol use disorders identification test (AUDIT) [36], Cannabis use disorder identification test – Revised (CUDIT-R),[37] Beck anxiety inventory (BAI) [38], General Anxiety Disorder-7 (GAD-7) [39], patient health questionnaire-9 (PHQ-9) [40–42], PTSD checklist – Civilian (PCL-C), Pittsburg sleep quality index (PSQI), DSM-5 Adult ADHD Checklist – Self-report [43], daily Stress inventory (DSI), the migraine disability assessment test (MIDAS), and Headcount-12 months.[44–46] Participants who screen positive for DSM-5 ADHD checklist will undergo the Adult ADHD Investigator Symptom Rating Scale (AISRS).

### Symptom checklist

At each timepoint, the post-concussion symptom scale, as a subset of the Sports Concussion Assessment Tool 5 [47], will be used to assess the presence and severity of concussion symptoms.

### 24-Hour dietary recall

Dietary recall will be conducted by the Automated Self-Administered 24-hour dietary assessment tool (ASA24) [48], Exploratory analysis may consider potential mediation or moderation effects of dietary intake, including total calories per carbohydrate, protein, and fat.

### Blood biomarker assessment

Capillary blood sampling using the Tasso blood collection device will be performed each test session. A trained phlebotomist will thoroughly clean the area with an alcohol swab and collect two sets of 400 uL of capillary blood sample using the Tasso device. Plasma levels of NF-L, Tau, UCH-L1, and GFAP will be assessed by Simoa 4-plex assay kits (Quanterix), as well as various exploratory markers including inflammatory cytokines and energy-related metabolites.

### Neuroimaging assessment

Neuroimaging assessments will take place in the Indiana University’s Imaging Research Facility (IRF), which houses a research-dedicated 3T Siemens Prisma MRI scanner equipped with a 64-channel head/neck coil.

High-resolution anatomical images (T1 weighted) will be acquired using 3D MPRAGE pulse sequence: TR/TE=2400/2.3ms, TI=1060ms, flip angle=8, field-of-view=256mm, matrix=320x320, bandwidth = 160 Hz/pixel, iPAT=2, resulting in 0.8 mm isotropic resolution. Two consecutive DTI sessions with opposite phase encoding directions will be performed with a simultaneous multi-slice (SMS) single-shot spin-echo echo-planar imaging (EPI) pulse sequence (TE=89.4ms; TR=3590s, 1.5mm isotropic resolution). Each session has 103 images with different diffusion weightings and gradient directions (7 b=0 s/mm^2^, 6 directions with b=500 s/mm^2^, 15 directions with b=1000 s/mm^2^, 15 directions with b=2000 s/mm^2^, and 60 directions b=2500 s/mm^2^). The DTI protocol is adapted from the Adolescent Brain Cognitive Development study,[49] which is optimized for analysis. The total scan time is 13 minutes. Resting-state data will be collected using a SMS single-shot EPI sequence with the following parameters: FOV=216mm, TR/TE=800/30ms, flip angle=52°, matrix=90×90, resolution=2.4 mm isotropic, and multiband acceleration factor=6, with 1000 total volumes acquired. Resting-state connectivity data will be acquired while the participant relaxes with eyes open and passively viewing a crosshair for 12 minutes. Two short spin-echo EPI scans with opposite phase encoding directions will be acquired for susceptibility artifact correction. Perfusion imaging will be acquired using three-dimension pulse continuous arterial spin labeling (3D-PCASL) perfusion imaging using a 3D background suppressed fast-spin-echo stack-of-spiral readout module with eight in-plane spiral interleaves (TR/TE/TI =5327ms/10.5ms/2525ms, labeling duration=1500ms, post-labeling delay=2525ms, no flow-crushing gradients, FOV=240x240mm2, in-plane matrix=128×128, number of excitation= 4, slice thickness=4mm) and an echo train length of 36 to obtain 36 consecutive axial slices [50]. Quantitative Susceptibility Mapping will be collected using a three-dimensional flow-compensated multiecho gradient-echo sequence with a repetition time of 45 msec, a total of five echoes (time of the first echo, 13msec) with echo spacing of 6 msec, flip angle=20°, FOV=24×24 cm, matrix=512×256, and 88 sections acquired with 1.5-mm thickness [51].

### Cold pressor test

The CPT procedure will take 30 min, and participants will rest quietly in the supine position the entire time. After 15 min of rest, the CPT will be performed by immersing the participant’s hand up to the wrist in agitated cold water (~0°C) for 2 min. Throughout, beat-to-beat blood pressure will be continually measured using finger photoplethysmography and heart rate using a 3-lead ECG. Data will be collected at 1,000 Hz using a data acquisition system (Powerlab), and mean values for MAP and heart rate will be extracted offline in 30 s bins. The area under the curve will then be calculated to provide an index of the cumulative sympathetic response to the CPT. Resting-state heart rate variability and spontaneous cardiovagal baroreflex sensitivity (cBRS) will be collected over the 5 min before the CPT. Using the R-R interval data collected from the ECG recordings during 5 min of paced breathing, time domain analyses will be performed to estimate overall heart rate variability and provide insight into cardiac parasympathetic activity [52]. Baroreflex sequences of 4 consecutive cardiac cycles will be captured using WinCPRS software. The mean of the regression slope will be calculated as the cBRS gain and used for analysis [53].

### Near point convergence (NPC)

NPC will be measured based on our established protocol [13–16]. Using the accommodative ruler, a target (14-point letter) will be moved toward the eyes at a rate of 1–2 cm/s. NPC will be recorded when participants report diplopia has occurred, or the tester observes eye misalignment. The assessment will be repeated twice, and the mean NPC value will be used for analyses.

### King-Devick test (KDT)

The KDT consists of a total of 145 saccades while rapidly reading numbers aloud to complete the test [54]. The KDT will be administered on a tablet. The total time (in seconds) will be used for analysis.

### Cognitive function

Cognitive function will be measured using the NIH Toolbox Cognition Battery, which has excellent reliability and validity to measure cognition in young adults [55], and has construct validity among those with TBI [56]. Multiple forms will minimize learning effects. This battery examines 5 cognitive domains (executive function, episodic memory, language, working memory, and processing speed) and takes 20 minutes to complete on a tablet [57,58].

### Ethics and dissemination

The trial will be conducted in accordance with the ethical principles outlined in the Declaration of Helsinki, 1996. This research was approved by the Indiana University Institutional Review Board (IRB #21334). Data will be collected using Research Electronic Data Capture (REDCap) spreadsheet to organize data and store in a secured database until statistical analysis is conducted. The data will be stored indefinitely for data quality purpose.

### Safety considerations and adverse events

There will be an independent safety monitor who will monitor adverse events data, oversee procedures designed to protect the privacy of participants, and report any adverse event. Data and safety monitoring will occur after every 5 participants have been enrolled. In the event of an adverse event, the safety monitor will prepare and submit a report to the IRB and will communicate between the team and IRB in any necessary investigation.

### Data analysis

#### Primary analysis.

A multivariable mixed-effect regression model (MMRM) will be used to analyze each aim separately to examine the protective effects of DHA+EPA against subconcussive neural injury. As mentioned, the primary time point is set to 24h post-heading. The models will account for repeated measures from the same participants. We expect changes in neurological outcomes (structural, physiological, autonomic impairments, cognition/N-O function) over time to differ between groups, which is reflected in the group (DHA+EPA vs. Placebo) by time (pre- vs. post-heading) interaction. Although we primarily treat time as a categorical variable (pre, 1^st^ 24h, 2^nd^ 24h, 7d, post), we will rerun the model by treating time as a continuous variable (post-heading length) as part of sensitivity analysis. All possible baseline covariates, such as demographics, omega-3 FA compositions, heading kinematics, psychiatric factors, and antioxidant levels, will be evaluated in the context of group difference.

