### Randomization and blinding

Using the *R* randomization function, randomly stratified IDs that correspond to study groups will be generated. Randomly stratified sequentially numbered IDs will be placed in sealed envelopes by a blinded statistician, and containers of identical appearance will be prepared by a study coordinator, who will oversee the allocation of correct supplementation. Participants will be blinded to their group assignment. For participants with a vegetarian diet, they will be nonrandomly assigned equally to each group.

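### Allocation is stratified, but the primary model does not commit to the stratification factors, and its group-difference rule, read as an imbalance screen, would rarely select them: precision may be lost, but no bias arises.

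*Protocol article*

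**What the plan says.** Under Randomization and blinding, the protocol article states that "randomly stratified IDs that correspond to study groups will be generated". It names no stratification factor, block size or ratio within strata. Vegetarians are handled apart from this ("they will be nonrandomly assigned equally to each group"), which is a separate matter.

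Under Primary analysis, each aim is analysed with a repeated-measures mixed model: "The models will account for repeated measures from the same participants". The effect of interest is the "group (DHA+EPA vs. Placebo) by time (pre- vs. post-heading) interaction", and "the primary time point is set to 24h post-heading". The candidate covariates are broad: "All possible baseline covariates, such as demographics, omega-3 FA compositions, heading kinematics, psychiatric factors, and antioxidant levels". The only rule on how they are used is that they "will be evaluated in the context of group difference". The sentence gives no threshold and does not mention the stratification factors. Sex becomes a named model term only under Secondary analysis. That section also describes comparing the two groups at the post-heading time points, chiefly the second 24-hour point and 168 hours.

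**The concern.** Stratified allocation makes the arms alike on the strata. That reduces the chance variation in the treatment contrast, but the analysis shows the benefit only if the strata are in the model. If they are left out, any between-stratum variation in the outcome analysed stays in the residual. The reported standard error is then larger than the true sampling error.

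The stated covariate rule pulls the wrong way. On its natural reading it looks for differences between the groups, and the stratification factors are the ones least likely to show any. At stake are interval width and power, not validity: the estimate stays unbiased and the test errs on the conservative side.

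**Working it through.** **1. The plan's own figures.** Sample size gives alpha 0.017 (0.05/3 = 0.0167, rounded), 90% power, and 90, 74 and 82 per group for Aims 1 to 3. It allows for 15% dropout and arrives at 104 per group. 90 × 1.15 = 103.5, which rounds up to 104, so the stated figure is reproduced; dividing 90 by 0.85 would give 106. No effect size is stated. Taking alpha as two-sided (an assumption), z(1 − 0.0085) = 2.387 and z(0.90) = 1.282, with sum 3.669. The effect implied for Aim 1 is 3.669 × √(2/90) = 0.547 SD.

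**2. Would an imbalance screen select the strata?** This was simulated with 208 participants, two strata, 15% random dropout and 4,000 runs. With blocks of 4 within strata, an imbalance at p < 0.05 occurred in 0 runs. With unrestricted allocation it occurred in about 6%. The article states neither block size nor threshold, so both are assumptions.

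**3. Does omission change the standard error of the primary contrast?** This was simulated with 90 per group, two equal and perfectly balanced strata, within-stratum SD 1, pre-post correlation 0.6, no treatment effect and 3,000 runs per scenario. All of these except the 90 are assumptions. The contrast is the group difference in change from pre-heading to 24 hours.

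| Stratum main effect (SD) | Stratum-by-time effect (SD) | SE without stratum | SE with stratum |
|---|---|---|---|
| 0, 0.5 or 1 | 0 | 0.133 | 0.133 |
| 1 | 0.25 | 0.134 | 0.133 (about +1% if omitted) |
| 1 | 0.5 | 0.138 | 0.133 (about +4%) |
| 1 | 1.0 | 0.153 | 0.133 (about +15%) |

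A stratum effect that is constant over time cancels from a within-participant change. One simulated data set with four time points and a 1 SD constant stratum effect, fitted as a mixed model, agrees: the interaction SE is 0.1236 with or without the stratum main effect.

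**4. Size in terms of R².** Let R² be the share of variance in pre-to-24 h change that the strata explain. The article gives no value, so 0 to 0.20 is assumed. With balanced strata left out, the model uses SE √(2/n), while the true sampling SE is √(1 − R²) times that. Hence:

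- SE overstatement = 1/√(1 − R²) − 1
- true alpha = 2 × [1 − Φ(2.387/√(1 − R²))]
- power without strata = Φ(1.282/√(1 − R²))
- power with strata = Φ(3.669/√(1 − R²) − 2.387)

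| R² | SE overstated | True alpha | Power without | Power with | Forgone (points) |
|---|---|---|---|---|---|
| 0 | 0% | 0.0170 | 90.0% | 90.0% | 0 |
| 0.05 | 2.6% | 0.0143 | 90.6% | 91.6% | 1.0 |
| 0.10 | 5.4% | 0.0119 | 91.2% | 93.1% | 1.9 |
| 0.20 | 11.8% | 0.0076 | 92.4% | 95.7% | 3.3 |

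Power without the strata rises above 90% because balanced allocation reduces the true sampling error even when the model does not credit it. A simulation at R² = 0.20 (20,000 trials) gave null rejection rates of 0.0078 without and 0.0167 with the strata, in line with the formula.

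The two calculations agree. Under step 3 the variance of change within strata is 2 × (1 − 0.6) = 0.8, and a stratum-by-time effect δ adds δ²/4. R² of 0.05 and 0.20 therefore correspond to δ of about 0.4 and 0.9 SD.

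**5. Post-only comparison.** Here a constant stratum effect does not cancel. With a 1 SD stratum main effect and no stratum-by-time effect, the SE is 0.167 without and 0.149 with the stratum (about 12% too large), and the rejection rate at 0.017 is 0.007 against 0.017.

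**The case against.** The covariate sentence is not plainly a selection rule. It could equally mean examining how covariates alter the estimated group difference, and it never says that a covariate enters only if the groups differ. The list of covariates is open and includes demographics, under which a stratum such as sex could fall. The article condenses a fuller protocol, and the final model terms may be fixed there or in a statistical analysis plan. All of this stands. A reader might infer that the strata can never qualify, or that the analysis ignores the stratification, but the document supports neither. The first needs restricted allocation within strata, which is not stated; the second is an inference from silence.

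A reader might also infer that the standard errors are too large across the board. Step 3 shows otherwise for the primary contrast. The R² values are also demanding. With two equal strata, a given R² needs a between-stratum difference in change of 2√R² total SDs, that is 0.45, 0.63 and 0.89 for 0.05, 0.10 and 0.20. The treatment effect implied for Aim 1 is itself 0.547, so the upper end of the range is an extreme case.

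What remains is narrower. The article does state a covariate rule, and on either reading that rule leaves the design factors uncommitted and the choice open to the data.

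**Conclusion.** The point holds as a modest matter of efficiency. The allocation is stratified, the primary model does not commit to the stratification factors, and the stated covariate rule, if used as an imbalance screen, would rarely choose them. There is no bias and no excess of false positives.

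For the primary group-by-time contrast the loss is nil when the stratum effect is constant over time. Over an assumed R² of 0 to 0.20, the standard error is overstated by 0% to about 12%, true alpha runs from 0.017 down to about 0.008, and 0 to about 3 points of power are forgone. The stated 90% is met throughout at 90 per group. The exposure is greater if the secondary comparisons at the later time points are made on post-heading values alone, because constant stratum effects then count too. These sizes rest on balanced strata, a two-sided alpha and assumed stratum effects; the article supplies none of the last.

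**What to change.** In Primary analysis, state that the factors used to stratify the IDs enter every primary and secondary MMRM as prespecified fixed effects with their interaction with time, whatever group difference is observed. Exempt them from the group-difference evaluation. The time interaction matters because a stratum main effect alone does nothing for the change contrast. Naming the factors in the same place would make the commitment checkable.

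The cost is a sentence or two and a few degrees of freedom out of about 180 completers (2 × 90). No new data are needed, because the strata are known at randomisation. The article reports that no participant had reached outcome data collection as of March 2025, so a change made early can be made without knowledge of results.

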#### Secondary analysis.

The cumulative effect from 2 heading sessions will be assessed using a MMRM by comparing 2 groups at post-heading time points, especially at 2^nd^ 24h and 168h. The role of female-related factors will be assessed by a series of MMRMs. Using a similar model structure to the primary analysis, sex (male vs. female) will be included as a term to analyze the potential group x sex interaction. We will then focus on female samples in each group to examine the potential phases of the MC (follicular vs. luteal) by group (DHA+EPA vs. placebo) interaction, and estradiol and progesterone levels will be incorporated as predictors. Lastly, the DHA+EPA group data will be stratified to assess whether there are subgroup differences [baseline DHA+EPA deficiency (<4% DHA+EPA) vs. sufficiency (≥4%)] in the outcomes, tested by the model similar to the first MMRM.

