### Outcome measures

Our primary outcomes (Table 1) will be assessed by comparing group differences, specifically group (DHA+EPA vs placebo) x time interaction, at 24-hour post heading relative to pre-heading baseline. Secondary outcome measures (Table 1) will be assessed beyond 24 hours post heading, including 24 hours post 2nd heading session, and up to 7 days after 2^nd^ heading session.

**Table 1 pone.0321808.t001:** Outcome Measures.

Outcome Measure	Type	Test/Task and Description
Blood Biomarkers	Primary Outcome	The primary outcome analyses will be comparing group differences (group x time interactions) in blood biomarkers, specifically NF-L (neurofilament light), tau (picogram per milliliter), GFAP (glial fibrillary acidic protein; nanograms per milliliter), UCH-L1 (ubiquitin C-terminal hydrolase-L1; picograms per milliliter), and S100B (S100 calcium binding protein B; nanograms per milliliter).
Diffusion Tensor Imaging (DTI)	Primary Outcome	DTI will be used to derive mean diffusivity (MD; square millimeters per second) and fractional anisotropy (FA; a unitless value that ranges from 0 to 1, 0 = Isotropic, 1= Anisotropic) as indicators joint of axonal integrity (axonal microstructure) and connectivity of white matter tracts by measuring how water molecules move through brain tissues.
Sympathetic Reactivity	Primary Outcome	Sympathetic Reactivity will be measured by the Cold Pressor Test (CPT). CPT is a general assessment of the ability of the sympathetic nervous system to become activated. The main metric will be changes in mean arterial pressure (MAP) following soccer headings. This test will be performed by submerging a participant’s hand into cold water for 2 minutes while autonomic and hemodynamic variables are recorded. At each data collection, participants will be instrumented for the measurement of heart rate (electrocardiogram) and continuous blood pressure. Participants will rest quietly for ~10 minutes before the CPT begins. The test takes 2 minutes.

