### Protocol proposal

#### Trial design.

This randomized placebo-controlled trial will consist of 2 groups: (1) DHA+EPA and (2) Placebo (Fig 2). Written informed consent will be obtained from all participants by the study coordinators. If individuals meet inclusion/exclusion criteria, pre-supplement baseline data will be gathered, including demographics, blood spot sample for assessment of omega-3 FA composition, dietary recalls for estimation of antioxidant intake, and symptom checklist. Participants will ingest DHA+EPA or placebo supplements daily throughout the 8-week supplementation phase and the subconcussion intervention phase. Participants in both groups will be required to ingest the supplement while monitored virtually, via Zoom or Facetime. Female participants’ menstrual cycle (MC), as determined by self-report, which will be further validated by salivary progesterone levels, will be monitored during the supplementation phase to determine regular or irregular MC and MC phases. During the biweekly visit, a blood spot sample will be collected to measure DHA+EPA levels and other FAs in the blood. During the subconcussion intervention phase, participants will be fitted with a wrist-worn Actigraph to monitor their activity/sleep levels. The subconcussion intervention will involve performing 20 controlled soccer headings per session. Participants will undergo 2 sessions in a 2-day period. Blood sample, MR data, autonomic reactivity, and clinical measures (symptoms, oculomotor, cognition) will be collected at pre-heading and 24-hour post-1^st^ session, 24-hour post-2^nd^ session, and 7-day post-2^nd^ session. Fig 1 indicates the current status of enrollment and Fig 2 depicts the study flow.

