### Sample size

Based on the sample calculation for each aim, we will recruit a minimum number of subjects needed to conduct all aims. Thus, 208 participants (n=104 per primary group) will be recruited. *Alpha level setting:* The primary groups (DHA+EPA vs. placebo) share 3 post-heading time points (1^st^ 24h, 2^nd^ 24h, 168h), which will be compared to the pre-heading baseline. Thus, we set the alpha level at 0.017 to account for multiple comparisons. Based on the estimated effect sizes and alpha level, a sample size of 90 (Aim 1), 74 (Aim 2), and 82 (Aim 3) per primary group will result in 90% power to detect the supplementation effect. We accounted for a dropout rate of 15%, resulting in n=104 per group needed to accomplish all aims.

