Our data will provide mechanistic insights as to how acute subconcussive head impacts induce sympathetic hyperreactivity. A meta-analysis concluded that DHA and EPA supplementation (3-4g/day) results in a decrease in blood pressure [25], which can be modulated by both autonomic and vascular origins. DHA+EPA supplementation (3.4g/d) for 8 weeks has been shown to lower sympathetic reactivity and attenuate the MAP response during the CPT [27]. Acute subconcussive head impacts have been shown to negatively influence autonomic function by triggering sympathetic hyperreactivity. We predict that 8 weeks of DHA and EPA pretreatment will prevent sympathetic hyperreactivity and attenuate the rise in MAP during the CPT not only after a single session of soccer headings, but also after 2 sessions. If our hypothesis is confirmed, DHA and EPA have a potent protective function for the autonomic nervous system against repetitive subconcussive head impacts.

The results obtained from this study will be valuable insights into combined effect of DHA and EPA on brain molecular, cellular, and physiological health in the context of subconcussive head impacts. Furthermore, these findings will pave the way for a large-scale longitudinal randomized clinical trial, serving as empirical evidence to inform the development of preventative guidelines for athletic organizations.

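### The cumulative-effect analysis names no pre-heading reference and conflicts with the Sample size section; read literally, it could not separate a supplementation effect from protection against heading

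*Protocol article*

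**What the plan says.** Four places in the protocol article bear on the contrast.

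- **Data analysis, Secondary analysis.** The cumulative effect is to be "assessed using a MMRM by comparing 2 groups at post-heading time points", with emphasis on the second 24 h visit and 168 h. No change score, interaction or pre-heading reference is named. Later in the same paragraph, the sex analysis and the baseline-deficiency analysis are each tied to the structure of the primary model; the cumulative-effect sentence is not.
- **Data analysis, Primary analysis.** Time is categorical with pre-heading as one of its levels. The expected effect is a difference between groups in change over time, "which is reflected in the group (DHA+EPA vs. Placebo) by time (pre- vs. post-heading) interaction".
- **Outcome measures.** The primary outcomes are assessed as group by time "at 24-hour post heading relative to pre-heading baseline".
- **Sample size.** The alpha of 0.017 is justified by three post-heading time points (first 24 h, second 24 h, 168 h), "which will be compared to the pre-heading baseline".

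Two further statements show why the reference matters. Under Trial design: "Participants will ingest DHA+EPA or placebo supplements daily throughout the 8-week supplementation phase and the subconcussion intervention phase". In the Discussion, 3.4 g/d, which is the trial's own dose, "for 8 weeks has been shown to lower sympathetic reactivity and attenuate the MAP response during the CPT".

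**The concern.** In most randomised trials the baseline precedes treatment, so comparing groups on post-baseline levels estimates the treatment effect without bias. Here the pre-heading visit comes after 8 weeks on different supplements. Randomisation balances the groups before supplementation, not at the pre-heading visit. A group difference in level at the second 24 h visit or at 168 h is therefore the sum of two things: whatever supplementation had already changed before any ball was headed, and any difference in how the groups respond to heading. Only the second is protection against head impacts.

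For the CPT outcome this is more than a theoretical worry. The Discussion cites evidence that the same dose for the same duration attenuates the MAP response, without reference to heading. It then predicts an attenuated MAP rise after two sessions and would read that as a protective effect. A level contrast could confirm the prediction even if heading affected both groups equally.

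**Working it through.** **The plan's own figures.** Alpha: 0.05 / 3 = 0.0167, which rounds to the stated 0.017. Evaluable numbers per group are 90 (Aim 1), 74 (Aim 2) and 82 (Aim 3), each for 90% power. The effect sizes behind them are not given. Solving backwards for Aim 3 with a two-sided test, d = (2.387 + 1.282) × √(2/82) = 0.573 SD. Nothing below changes these figures.

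**What each contrast estimates.** Let s be the group difference at the pre-heading visit due to supplementation, assumed to persist through the heading week because supplementation continues. Let h be the group difference in response to heading.

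- Level contrast at a post-heading visit: expected value s + h.
- Change from pre-heading (group by time): (s + h) − s = h.

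With h = 0 the level contrast has expected value s, and the change contrast has expected value 0.

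**Inputs for the illustration.**

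- n = 82 per group (Aim 3, Sample size section), because the CPT is the outcome with cited evidence of a supplementation effect.
- Alpha 0.017 (Sample size section). Two-sided is assumed, since sidedness is not stated.
- h = 0 (assumed).
- s = 0.2 to 0.5 SD (assumed; the article gives no size).

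**Formula.** The two-sample t-test has 2 × 82 − 2 = 162 degrees of freedom, critical value 2.412 and noncentrality s × √(82/2) = 6.403 × s. The probability of significance is P(|T| > 2.412) under that noncentral t distribution.

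| s (SD) | Noncentrality | Level contrast significant | Change contrast significant |
|---|---|---|---|
| 0.2 | 1.281 | 13.2% | 1.7% |
| 0.3 | 1.921 | 31.5% | 1.7% |
| 0.4 | 2.561 | 56.0% | 1.7% |
| 0.5 | 3.202 | 78.4% | 1.7% |

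The normal approximation gives nearly the same results: 13.4%, 32.1%, 56.9% and 79.2%.

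**Simulation check.** With 90 per group, 20,000 runs per setting and pre-post correlations of 0.5 and 0.9, the change contrast rejected in 1.6% to 1.8% of runs for every s tried (0, 0.2, 0.3, 0.5). The level contrast rejected in about 14% to 15%, 35% and 83% of runs at 0.2, 0.3 and 0.5 SD. This agrees with the formula at that sample size.

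**The texts side by side.** The Sample size section refers the second 24 h visit and 168 h to pre-heading. The Secondary analysis section, where the analysis is defined, compares groups at those visits and stops there. Having pre-heading as a level of time in the MMRM does not settle the matter, because a four-time-point model can yield either levels or changes.

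**The case against.** The strongest reply is that the article already supplies the reference. The Sample size section lists the two visits in question and compares them with pre-heading, and the Primary analysis section has pre-heading in the model and speaks of change over time. Table 1 also describes the main CPT metric as changes in MAP after headings. On that reading the secondary sentence merely says that the same model is read at later visits, and a condensed journal article need not repeat the contrast. Much of this stands. It is why a reader who infers that the trial is committed to a level comparison, and will report a supplementation effect as protection against two sessions, goes further than the text allows. It does not remove the conflict: the statement in the Sample size section justifies an alpha level, whereas the Secondary analysis section states a specific contrast, and the two differ.

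Three further limits are accepted.

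- The article cites a supplementation effect separate from heading only for the MAP response to the CPT among the measured outcomes at issue. It gives no comparable evidence of a pre-heading difference for the blood biomarkers or diffusion measures.
- A reader might infer that the analysis fails because it does not isolate the second session. But the cumulative effect of two sessions can mean their total effect, and the Discussion's use of the term fits that. An increment contrast is an option, not a correction.
- A reader might also infer a loss of power from dropping the within-person comparison. That depends on the literal reading and on pre-post correlations that the article does not give, so it is not relied on here.

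**Conclusion.** The point holds as an unreconciled conflict about the reference for the cumulative-effect contrast. The Secondary analysis wording, followed literally, is a level comparison that cannot tell a supplementation effect present before heading from protection against two sessions. The Sample size section points to a change from pre-heading. Left as it is, either contrast could be presented as the planned one once the data are known.

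Misattribution is therefore a risk, not a certainty, and it is documented only for the CPT outcome. Its size depends on a pre-heading difference that the article does not state. Over an assumed 0.2 to 0.5 SD, with 82 per group, two-sided alpha 0.017, a constant supplementation difference and no heading effect, the chance of a significant level contrast runs from 13.2% to 78.4%, against 1.7% for the change contrast.

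The wording should be corrected, but the reach is limited. The primary 24 h contrast is already an interaction relative to pre-heading, and no sample-size figure changes.

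**What to change.** Reword the cumulative-effect sentence in the Secondary analysis section along these lines: the cumulative effect will be estimated from the same four-time-point MMRM as the primary analysis, as the group by time contrasts of change from pre-heading to the second 24 h visit and from pre-heading to 168 h. Add that the group difference at the pre-heading visit will be reported separately, as the effect of supplementation alone. This brings the section into line with the Primary analysis and Sample size sections.

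If the added effect of the second session is of interest, a group by time contrast of the second 24 h visit minus the first 24 h visit can be taken from the same model. This is optional.

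The cost is one or two sentences and a different set of contrasts from a model that is to be fitted anyway. No new data, visits or participants are needed. The change should be made before any unblinded outcome data are examined.
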